### Ethical issues

This study has been approved by the Institutional Review Board of Longhua Hospital, Shanghai University of TCM on November 30^th^ 2011 (No: 2011LCSY031). All study participants will sign the written informed consent prior to participation. All patients will receive written and oral reassurance regarding the typical benign course of the symptoms. We will explain that placebo and treatment with Qishe Pill might be equally effective interventions. Patients in all treatment groups will be allowed to use painkillers when necessary. In general, paracetamol is selected with or without a non-steroidal anti-inflammatory drug. Patients will be asked to note their drug use, including over-the-counter analgesics, in a specially designed diary during the first four weeks following randomization.

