Patients will be recruited from May 2012 to Oct 2013 from the five sites in China. The review board at each institution approved the protocol. The study is organized and coordinated by Longhua Hospital, Shanghai University of TCM in Shanghai, China.

This study is to be conducted according to the protection of patients, as outlined in the Declaration of Helsinki, and approved by the appropriate Institutional Review Boards. Each participant will sign the written informed consent before undergoing any examination or study procedure, in compliance with Good Clinical Practice. Patients who initially meet these eligibility criteria are then to complete the additional baseline testing and will be randomized into either the treatment or the control group. An independent steering committee will oversee the study.

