### Sample size considerations

We calculated the sample size for this two arm trial on the basis of the comparison treatment (Qishe Pill) versus placebo, with equal allocation in the treatment arms and five repeated measurements (at entry, at 2 and 4 weeks’ treatment, and at 2 and 5 months’ follow-up), with an estimated correlation coefficient of the measurements of ρ=0.8 and a difference in the mean value of the VAS for neck pain of 12 mm, as a clinical relevant difference with an estimated standard deviation in each treatment group of 25 mm [10]. As neck pain is the main complaint in cervical radiculopathy, we chose this outcome to calculate the sample size. Under the setting of alpha = 0.05 and power = 90%, the calculated sample size of each group is around 96. Considering 20% loss to follow-up, the total sample size needed to detect this difference at a 5% level of significance with a power of 90% is 240 patients.

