### Statistical analysis

The data will be collected and analyzed according to the intention-to-treat principle. Standard statistical techniques will be used to describe characteristics of patients in both groups. We will compare baseline characteristics in both groups and if incomparability appears, we will perform the secondary analysis, adjusting for differences. The primary outcome, amount of pain, will be compared between both groups using survival analysis and analysis of variance for repeated measures. If adjustment for possible baseline incomparability is needed, analysis of covariance will be performed. We will use multivariate analysis to do retrospective analysis with the baseline data of the effective cases and ineffective cases in the treatment group. Differences in the baseline data will be used to optimize the inclusion criteria. We will do subgroup analysis based on severity of pain (VAS=70 mm) and use of analgesics.

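### Comparing effective with ineffective cases in the Qishe Pill arm alone cannot separate prognosis from response to the pill, so inclusion criteria built on it could be mis-set

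*Protocol article*

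**What the plan says.** The protocol article's Statistical analysis section fixes a method and a use for it in consecutive sentences. The method is: "We will use multivariate analysis to do retrospective analysis with the baseline data of the effective cases and ineffective cases in the treatment group". The use is: "Differences in the baseline data will be used to optimize the inclusion criteria".

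The treatment group here is the Qishe Pill arm. The section on patient population and recruitment says that patients "will be randomized into either the treatment or the control group", and the sample size section names Qishe Pill as the treatment that is compared with placebo. No placebo counterpart and no interaction term is stated for this analysis.

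The same section plans a separate analysis: "We will do subgroup analysis based on severity of pain (VAS=70 mm) and use of analgesics". It is not linked to the inclusion criteria.

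Two statements under Ethical issues bear on the point. Patients are to receive "reassurance regarding the typical benign course of the symptoms", and "Patients in all treatment groups will be allowed to use painkillers when necessary".

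**The concern.** To improve inclusion criteria for a drug, one needs to know which patients gain more from the drug than they would have gained without it. A patient on the pill who improves may have improved through the natural course, through painkillers, or because pain was unusually bad on the day of entry. The article itself expects the first and permits the second. Comparing improvers with non-improvers among pill patients therefore mixes factors that predict a good course with factors that predict a response to the pill.

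What is at stake is the choice of patients for later study or use. Criteria could be narrowed on a factor that has nothing to do with the pill, or a real modifier could be missed. The trial has a randomised placebo group that can separate the two, and this analysis leaves it out.

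**Working it through.** **What each comparison estimates.** Let X be a standardised baseline factor. Write improvement on placebo as a + bX and improvement on the pill as a + d + (b + g)X. Here b is the prognostic slope, d the average pill effect at X = 0, and g the effect modification.

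- Pill arm only: the slope on X is b + g.
- Both arms, treatment-by-X interaction: (b + g) − b = g.

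Only g bears on who gains from the pill. Multivariable adjustment within the pill arm separates one baseline factor from another; it does not separate b from g for any of them.

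**Inputs.** From Sample size considerations: 96 per group before loss to follow-up, "a difference in the mean value of the VAS for neck pain of 12 mm", and "estimated standard deviation in each treatment group of 25 mm". The article gives no figure for this analysis, so there is none to reproduce.

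Assumptions not in the document:
- effective means at least 20 mm improvement;
- mean improvement is 8 mm on placebo, hence 8 + 12 = 20 mm on the pill;
- the 25 mm SD applies to improvement;
- one factor is tested at a time at two-sided 5%.

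**Simulation, 2,000 trials per setting, 96 per arm.** The factor is purely prognostic (g = 0):

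| b, mm per SD | Correlation b/25 | Pill-arm comparison | Same, inert pill (d = 0) | Two-arm interaction |
|---|---|---|---|---|
| 5 | 0.2 | 36% | 33% | 4% |
| 7.5 | 0.3 | 67% | 62% | 5% |
| 10 | 0.4 | 89% | 85% | 5% |

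With 120 per arm, the pill-arm column becomes 42%, 77% and 96%.

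**Closed-form check, b = 7.5.** The cut at 20 mm equals the pill-arm mean, so half the arm is effective. The expected difference in X between effective and ineffective cases is 2 × 0.798 × 0.3 = 0.479. The within-group variance is 1 − (0.798 × 0.3)² = 0.943. With 48 per group the standard error is √(0.943 × 2/48) = 0.198. The ratio is 0.479/0.198 = 2.42, which gives a power of 67%, as simulated.

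**True modifiers, 96 per arm.**
- No prognostic effect, g = 7.5 or 10: the pill-arm comparison finds the factor in 63% or 84% of trials, the interaction test in 54% or 77%.
- Opposite prognostic effect of equal size (b = 7.5, g = −7.5; b = 10, g = −10): the pill-arm slope is zero. The pill-arm comparison finds the factor in 5% or 6%, the interaction test in 57% or 85%.

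**Sensitivity to the SD.** If the article's correlation of 0.8 held between baseline and outcome, the SD of change would be 25 × √(2 × 0.2) = 15.8 mm. A slope of 5 mm would then be a correlation of 5/15.8 = 0.32 instead of 0.2, so with the cut again near the pill-arm mean the pill-arm comparison would flag it more often.

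**The case against.** The strongest reply is that this is a side analysis with no bearing on the randomised comparison, the sample size or the safety conclusions, and that the percentages come from assumed inputs. Both statements are true. The 36% to 89% is also simply the power to detect a real prognostic association. It becomes an error rate only when the finding is read as response to the pill. The stated use of the result invites that reading, so the objection limits the weight of the point without removing it.

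The separate subgroup analysis might be thought to fill the gap. It covers only pain severity and analgesic use, is not tied to the inclusion criteria, and does not say how the arms enter it.

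A reader might also infer four stronger things that the document does not support.

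- **That the comparison shows prognosis and nothing else.** It shows the sum, and a true modifier can appear in it, as the 63% and 84% above show.
- **That eligibility will change within this trial.** The analysis is called retrospective, and Randomization and allocation keeps researchers blinded and leaves uncovering to a third-party statistical team. Trial status reports three sites finished and 28 and 30 enrolled at the other two. If the finished sites reached 48 each, that is 3 × 48 + 28 + 30 = 202 of 240. Later use is the natural reading, although the text does not say so.
- **That the new criteria would shrink the room for a treatment effect.** Under a purely prognostic factor the mean VAS difference is the same at every level of the factor, so selecting on it leaves the effect unchanged. Regression to the mean could even favour patients with high baseline pain.
- **That VAS is to be dichotomised.** The article does not say which outcome defines an effective case. My 20 mm cut is an illustration only.

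**Conclusion.** The concern holds in this form: the stated one-arm comparison cannot serve its stated purpose, because it estimates prognosis plus effect modification and cannot separate them. Criteria derived from it could be mis-set; that they would be is not shown. This is a defect in a method that the article fixes, together with its use, and not a detail left to a fuller document.

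The percentages depend on the assumed cut-off, placebo improvement, SD of improvement and prognostic slopes. The structural result, b + g against g, does not depend on them. The change should be made, but its weight is moderate because the analysis is secondary and the primary comparison is untouched.

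**What to change.** Replace the two sentences with wording such as: Effect modification will be explored in all randomised patients of both arms by treatment-by-baseline-covariate interactions, with VAS as a continuous outcome in the repeated-measures analysis. The covariates are a short list fixed before unblinding (for example baseline VAS, NDI, age and symptom duration). Results are hypothesis-generating and may inform the inclusion criteria of future trials.

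The text should name the repeated-measures analysis because the article lists both survival analysis and repeated-measures analysis of variance for the primary outcome. The covariates in the example are a suggestion; the investigators should choose them.

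The cost is a change of wording and agreement on the list, with no new visits or patients if the chosen factors are already recorded. The drawback is low power. In the simulation with b = 10, a modifier of 5 mm per SD in the opposite direction was found in 31% of trials at 96 per arm and 38% at 120 per arm. A non-significant interaction should therefore not be read as evidence that the pill works equally well in everyone; estimates with confidence intervals should be reported.

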### Patient population and recruitment procedure

All participants will be selected from the general outpatient clinic offive hospital sites, where the patients willbe diagnosed with cervical radiculopathy confirmed by a neurologist, and then diagnosed based upon clinical manifestations (pain along the cutaneous distribution of one or more cervical roots, which may include weakness and hyporeflexia), physical examination, and imaging [4].

Inclusion criteria are age between 18 and 65 years, pain or stiffness in the neck for at least 2 weeks, neck symptoms reproducible during physical examination, neck pain on neck disability index (NDI) of 18 or more, and radiation of arm pain distal to the elbow, plus at least one of provocation of neck or arm pain by neck movements, Brachial plexus traction test, foraminal compression test, or foraminal separation test, sensory changes in one or more adjacent dermatomes, or muscle weakness in one or more adjacent myotomes. Further inclusion prerequisites are willingness for treatment and to adhere to measurement regimens, no involvement in litigation, and written informed consent.

Excluded criteria are patients whose history, signs, and symptoms suggested a potential non-benign cause (including previous neck surgery) or evidence of a specific pathologic condition, such as malignancy, neurologic disease, fracture, herniated disc, or systemic rheumatic disease, clinical signs of spinal cord compression, previous neck trauma or treatment with surgery, obvious vertigo, pregnant women, lactating women, currently participating in other clinical trials, accompanied with hepatic, renal, hematopoietic system, endocrine system, cardiovascular, nervous system, primary and other serious diseases (serum ALT, AST, ALP, TBIL, DBIL, Cr or BUN more than two-fold than the upper limit of reference value), tuberculosis, vertebral deformities, cancer and mental illness, and insufficient understanding of the Chinese language, and/or have been treated with physical therapy or manual therapy for neck pain during the previous 2 weeks.

Patients with concurrent headaches, non-radicular pain in the upper extremities, and low back pain will not be excluded, but neck pain has to be the main symptom for all patients [8].

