### Outcome measurements

The primary study outcome is pain severity (measured with a visual analogue scale (VAS)). Secondary outcomes are a composite of functional status (measured by NDI), patient satisfaction, and adverse events as reported in the trial. The VAS measures the amount of pain, which is a pain score ranging from 0 (no pain) to 100 mm (very severe pain) [9]. Operationally, the VAS score is displayed as a horizontal line, 100 mm in length, with word descriptors anchored at each end. The patient marks on the line the point that they feel represents their perception of their current pain. The VAS score is then determined by measuring in millimeters from the left hand end of the line to the point that the patient marks. The VAS score and NDI will be measured at all the measurement points (baseline, 2 and 4 weeks of treatment duration, and 2 and 5 months of follow-up duration).

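### The severity subgroup cuts a continuous 0-100 mm pain score once at 70 mm, which loses information on effect modification if the effect changes gradually with pain

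*Protocol article*

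**What the plan says.** The Statistical analysis section gives the subgroup plan in one sentence: "We will do subgroup analysis based on severity of pain (VAS=70 mm) and use of analgesics". It does not say which VAS reading is split, on which side of the cut a score of exactly 70 mm falls, or whether an interaction test accompanies the subgroups.

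Under Outcome measurements the VAS is "a pain score ranging from 0 (no pain) to 100 mm (very severe pain"), and "The VAS score is then determined by measuring in millimeters from the left hand end of the line to the point that the patient marks". Further on, that section says "The VAS score and NDI will be measured at all the measurement points (baseline, 2 and 4 weeks of treatment duration"), with follow-up readings at 2 and 5 months. Table 2 also schedules a VAS at Visit 1, before medicine is first issued at Visit 2.

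The severity entry criterion is set on another instrument: "neck pain on neck disability index (NDI) of 18 or more". There is no minimum VAS for entry, and no expected mean VAS or share of patients above 70 mm is given. The Sample size considerations supply the only spread, "an estimated standard deviation in each treatment group of 25 mm", which is not expressly a baseline SD.

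**The concern.** A severity subgroup analysis is there to show whether the effect differs with how much pain the patient starts with. A single cut treats patients at 69 and 71 mm as different kinds of patient and those at 20 and 69 mm as the same kind. If the effect rises or falls gradually with pain, much of the evidence for that lies within the two groups, where the split cannot use it.

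With no VAS entry criterion, nothing places 70 mm near the middle of the enrolled scores. If most patients score lower, the upper group is small, its estimate is imprecise, and the loss grows. The trial was sized for an overall difference of 12 mm and not for effect modification, so information on this question is scarce to begin with.

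**Working it through.** **Plan's own figure.** The article gives no figure for the subgroup analysis, so there is none to reproduce. The calculation shows what a 70 mm cut keeps compared with using the score in millimetres.

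**Inputs from the article.** SD 25 mm; correlation between measurements 0.8; about 96 patients per group, so 2 × 96 = 192 analysed, which is also 240 × 0.8; "Under the setting of alpha = 0.05 and power = 90"%.

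**Assumptions.** The split uses the baseline VAS. Baseline VAS is normal with SD 25 mm and a mean between 45 and 70 mm. The effect is linear in baseline VAS. One post-baseline visit is analysed with baseline as covariate, with a two-sided 5% test.

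**Step 1: information kept.** For a linear gradient, the share kept by a cut is the squared correlation between the score and the indicator of being above the cut. For a normal score this is φ(z)² / [p(1−p)], with z = (70 − mean)/25 and p = P(Z > z).

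- Mean 70: z = 0, p = 0.50; 0.3989² / 0.25 = 0.637. Loss 36%.
- Mean 45: z = 1, p = 0.159; 0.2420² / (0.159 × 0.841) = 0.439. Loss 56%.
- Means 50, 55, 60 and 65: share kept 0.50, 0.56, 0.60 and 0.63.

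For the same precision on a linear gradient, the split would need 1/0.637 = 1.57 to 1/0.439 = 2.28 times as many patients.

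**Step 2: power.** The standard error of the continuous interaction, per SD of baseline VAS, is 2 × 25 × √(1 − 0.8²) / √192 = 30 / 13.86 = 2.17 mm. With 80% power it detects 2.80 × 2.17 ≈ 6.1 mm per SD. Power of the cut for the same gradient is Φ(2.80 × √share − 1.96):

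- Mean 70: Φ(2.80 × 0.798 − 1.96) ≈ 61%.
- Mean 45: Φ(2.80 × 0.662 − 1.96) ≈ 46%.

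A simulation with 96 per arm and a gradient of 0.28 mm per mm (7 mm per SD) agrees in direction. It gave 89% for the continuous test against 71% for the cut at mean 70, and 88% against 54% at mean 45.

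**Step 3: sensitivity to the gradient.** At 3 mm per SD, 3/2.17 ≈ 1.39. The continuous test has Φ(1.39 − 1.96) ≈ 28% power and the cut about 15-20%. Both are weak and the gap is 8-13 points.

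**Step 4: sensitivity to the distribution.**

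| Baseline VAS | Loss |
|---|---|
| Normal, 10% above 70 mm | 66% |
| Normal truncated to 0-100 mm, means about 45-75, SDs about 11-22 | about 33% to 89% |
| Uniform 0-100 mm | 37% |
| Uniform 40-100 mm | 25% |

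Under a linear gradient every case shows a loss, but its size depends on facts the article does not give.

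**The case against.** The strongest case against has four parts.

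- A condensed article may leave the reason for the cut and the form of the subgroup test to a full protocol or analysis plan. A reader might infer that 70 mm is arbitrary, or that the split is an error. The article does not support either: it simply gives no reason, and a cut named in advance is common practice and limits data-driven choice. What remains is that the article does publish one specific split, and that choice can be assessed.
- No interaction test is named, so the split may be meant only for display. This stands. The power comparison shows what the split would give if it were used to judge severity dependence; it does not describe a test in the plan.
- Baseline is an inference. It is the natural reading of pain severity, and a pre-treatment score is scheduled, but the section names no time point. A reader might equally infer a subgroup formed on a post-randomisation score; nothing in the article says so.
- The power gap in step 2 needs a steep gradient: 6.1 mm per SD is about half the whole 12 mm target difference. For 3 mm per SD both approaches are underpowered, so the gain should not be oversold.

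Also, the sample size section counts the entry VAS among the five repeated measurements. It therefore cannot simply be added as a covariate to a model in which it is already an outcome.

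**Conclusion.** The point holds as a minor, low-cost improvement to a stated analysis choice. If the effect changes roughly linearly with baseline pain, the 70 mm split loses about 36% of the information on effect modification for a normal score cut at its mean, and about 56% with mean 45 mm and SD 25 mm.

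It would be tempting to read 36-56% as a property of this trial. The documents do not support that: the baseline mean is not given, the 25 mm SD is not expressly a baseline value, and other distributions move the loss from about 25% to well above 60%. If the effect truly changes at about 70 mm, the loss does not apply. Neither the primary comparison nor the sample size is affected.

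**What to change.** In the Statistical analysis section, state which VAS reading defines severity and add a supportive analysis:

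- Model the post-baseline VAS scores with treatment, Visit 1 VAS as a continuous covariate, and their interaction. The entry VAS must not also be an outcome in this model.
- Report the treatment difference with its 95% CI at several baseline values, for example 30, 50 and 70 mm.
- Check linearity with a quadratic or spline term.
- Keep the groups below 70 mm and at or above 70 mm as a descriptive display.

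This needs no new data or patients. The cost is the linearity assumption, which can be checked, and slightly more analysis work, because the supportive model treats the entry score differently from a repeated-measures analysis that includes it as an outcome. The primary comparison need not change.

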### Study schedule

The measurements that need to be performed at each visit are listed in Table 2.

**Table 2 T2:** Study schedule of clinical trial (6 months)

	**Initial screening**		**Treatment times**		**Follow-up**	
	**Visit 1**	**Visit 2**	**Visit 3**	**Visit 4**	**Visit 5**	**Visit 6**
	**Week 0**	**Week 1**	**Week 2**	**Week 4**	**Month 2**	**Month 5**
Determined the exclusion criteria	Yes					
Informed consent	Yes					
Randomized	Yes					
Weight	Yes		Yes	Yes		
Blood pressure	Yes		Yes	Yes		
Heart rate/Rhythm	Yes		Yes	Yes		
Respiratory rate	Yes		Yes	Yes		
Spurling’s test	Yes					
Brachial plexus force test	Yes					
Drug allergy history	Yes					
Blood routine	Yes			Yes		
Urine routine	Yes			Yes		
Excrement routine	Yes			Yes		
Occult blood	Yes			Yes		
ECG	Yes			Yes		
Liver function test	Yes			Yes		
Kidney function test	Yes			Yes		
X-ray (frontal and lateral)	Yes			Yes		
Concomitant medication		Yes	Yes	Yes		
VAS scores	Yes	Yes	Yes	Yes	Yes	Yes
NDI scores	Yes		Yes	Yes	Yes	Yes
SF-36 scores		Yes	Yes	Yes		
The medicine issue		Yes	Yes			
Compliance assessment			Yes	Yes		
Degree of satisfaction				Yes		
Safety evaluation		Yes		Yes		

ECG: Electrocardiogram; VAS: Visual analogue scale; NDI: Neck disability index: SF-36: The MOS item short from health survey.

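### The analgesic subgroup has no time point, and the only analgesic data described are post-randomisation, so if the pill reduces pain both subgroup effects are biased, generally downwards

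*Protocol article*

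**What the plan says.** The Statistical analysis section commits to two subgroup factors in one sentence: "We will do subgroup analysis based on severity of pain (VAS=70 mm) and use of analgesics". Neither factor is given a time point.

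Three other places show what analgesic information the trial collects:

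- **Ethical issues.** "Patients in all treatment groups will be allowed to use painkillers when necessary", and patients note their drug use, over-the-counter products included, "in a specially designed diary during the first four weeks following randomization".
- **Study schedule (Table 2).** The row "Concomitant medication" is ticked at Visits 2, 3 and 4 (Weeks 1, 2 and 4). It is blank at Visit 1 (Week 0), the visit at which randomisation is ticked.
- **Patient population; Randomization and allocation.** Earlier analgesic use is neither an eligibility criterion nor a stratification factor. The only recent-treatment exclusion concerns patients who "have been treated with physical therapy or manual therapy for neck pain during the previous 2 weeks".

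The general analysis principle is stated as "The data will be collected and analyzed according to the intention-to-treat principle".

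**The concern.** A subgroup comparison keeps the protection of randomisation only if treatment cannot influence who belongs to the subgroup. Painkillers taken as needed during treatment fail that test when the treatment under study is meant to relieve the same pain.

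If the pill works, some patients who would have taken painkillers on placebo do not take them on the pill. The users left in the active arm are those whose underlying pain is worse, so they are set against a less severe group of placebo users. The non-users in the active arm now include patients with worse underlying pain than the placebo non-users. Both comparisons are tilted against the pill.

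What is at stake is interpretation. A reader could see a modest effect in users and a modest effect in non-users, and conclude that the pill adds little either way, while the randomised comparison shows the full effect.

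**Working it through.** **Step 1: which analgesic variable the plan can use.** The diary starts at randomisation, and the medication row of Table 2 starts at Week 1. No pre-randomisation analgesic measure is described. As written, the subgroup would be built from use after randomisation. This is an inference from two sections, because the subgroup sentence itself is silent on timing.

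**Step 2: inputs.** From Sample size considerations: effect δ = 12 mm, SD σ = 25 mm, correlation between measurements ρ = 0.8. The article gives no figure for the following, so they are assumed:

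- placebo mean pain: 60 mm in model A, 45 mm in model B;
- a patient takes painkillers when pain plus a personal deviation (normal, SD τ) exceeds a trigger c;
- τ sets how closely use follows pain: small τ means closely, large τ means loosely.

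The plan states no figure for the subgroup effects, so there is none to reproduce.

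**Step 3: formula.** Let s = √(σ² + τ²), let m be the arm's mean pain when the painkiller decision is made, and z = (c − m)/s. With φ and Φ the standard normal density and distribution function, and M the arm's mean pain at the analysed visit:

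- mean in users = M + k·φ(z)/(1 − Φ(z))
- mean in non-users = M − k·φ(z)/Φ(z)

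Here k = σ²/s when the decision and the outcome refer to the same pain (model A), and k = ρσ²/s when Week 2 pain drives use and Week 4 pain is the outcome (model B).

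**Step 4: one case in full** (model A, c = 60, τ = 10). s = √(625 + 100) = 26.93 and k = 625/26.93 = 23.21.

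- Placebo: z = 0, and 50% are users. Users 60 + 23.21 × 0.3989/0.5 = 78.52. Non-users 60 − 18.52 = 41.48.
- Active: m = 48, z = 12/26.93 = 0.446, and 32.8% are users. Users 48 + 23.21 × 0.3612/0.3279 = 73.57. Non-users 48 − 23.21 × 0.3612/0.6721 = 35.52.
- Apparent effect: users 78.52 − 73.57 = 4.95 mm; non-users 41.48 − 35.52 = 5.96 mm. The true effect is 12 mm in every patient.

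**Step 5: the range.** True effect 12 mm throughout. Model A uses triggers 50, 60 and 70 mm; model B uses 35, 45 and 55 mm, with the full effect already present at Week 2.

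| Model | Link of use to pain | Users, mm | Non-users, mm |
|---|---|---|---|
| A | close, τ = 10 | 4.3–5.8 | 5.1–7.0 |
| A | τ = 25 | 7.7–8.3 | 8.0–8.8 |
| A | loose, τ = 50 | 10.3–10.5 | 10.4–10.6 |
| B | exact, τ = 0 | 4.8–6.2 | 5.6–7.4 |
| B | loose, τ = 50 | 10.7–10.8 | 10.7–10.9 |

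Simulation of model A with 2,000,000 patients per scenario agrees to within 0.1 mm. The extremes are 1 − 4.3/12 = 64% and 1 − 10.9/12 = 9%, so about 60% down to about 10%.

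**Step 6: conditions that reduce or remove the bias.**

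- True effect zero: about 0 mm in both subgroups, so no bias.
- Model B, τ = 0, placebo mean 50 mm, only 4 mm of effect at Week 2: 9.6–10.4 mm in both subgroups.
- The same with no effect yet at Week 2: 12.0 mm in both.
- Use driven by baseline pain instead of on-treatment pain (simulated): 12.0–12.1 mm in both. The fault therefore lies in the timing of the variable, not in subgrouping by analgesics as such.

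**The case against.** The strongest reply is that the subgroup sentence never says post-randomisation use. The 70 mm factor beside it also lacks a time point, and a journal article may omit a medication history that the case report form holds. This stands in part: the timing is inferred, and the plan cannot be said to declare a post-randomisation split. But the article names the subgroup and describes only one source for it, and that source begins at randomisation.

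A second reply is that Table 2 first issues medicine at Visit 2, where concomitant medication is also ticked, so that record might precede the first dose. Table 2 places Visit 2 at Week 1, after randomisation at Week 0, and nothing ties the subgroup to that record.

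Third, a sharp pain trigger is close to a worst case. Habit, tolerance and access also determine who takes painkillers. This stands, and is why the range reaches down to about 10%.

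Three stronger readings are tempting and not supported:

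- **Both subgroups lose 40–60% of the effect.** That holds only when use follows pain closely and the full effect is present when painkillers are taken.
- **Information on analgesic sparing is lost.** The diary and the Week 1, 2 and 4 records still collect it, and it can be compared between arms.
- **The split creates a marked false interaction.** In the scenarios above, the gap between users and non-users is at most about 2.7 mm.

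**Conclusion.** The point holds in a conditional form. The analgesic subgroup is undefined in time, and the only data described for it are a possible consequence of treatment. If the pill changes pain and thereby painkiller use, both subgroup effects are biased, generally towards understatement, by about 10% to 60% of a true 12 mm effect. If treatment does not change analgesic use, the bias is zero.

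The direction follows from the trial's own hypothesis. The size rests on an assumed placebo mean, pain trigger and strength of link between pain and use, none of which the article gives.

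A reader might infer that the trial's main result is compromised. It is not: the primary intention-to-treat comparison is not split by analgesic use, and the sample size does not depend on this subgroup. The analysis should be corrected, but the defect is confined to one secondary sentence.

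**What to change.** In the Statistical analysis section:

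1. Define the analgesic subgroup by use documented before randomisation, either by adding concomitant medication at Visit 1 in Table 2 or by taking it from recorded history. Where no such record exists, drop the subgroup.
2. Report on-study analgesic use by arm as an outcome, from the diary data already collected.
3. State that the 70 mm severity split uses baseline VAS, which Table 2 already schedules at Visit 1.

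The cost is a few lines of analysis wording and one tick in Table 2, with no effect on the primary analysis or the sample size. The downside is that patients already enrolled may lack a pre-randomisation record. By the Trial status section, three sites have finished recruiting and the other two have 28 and 30 patients. If each finished site reached its planned 48, that is 3 × 48 + 28 + 30 = 202 of 240, so a new Visit 1 entry would reach at most 38 patients. Unless earlier use can be recovered from existing records, dropping the subgroup is the realistic outcome.
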